Moreover, meta-analysis and systematic reviews have indicated that low-frequency rTMS applied to the dorsolateral prefrontal cortex is safe and has the potential to alleviate insomnia symptoms and sleep disturbance in different neurological and neuropsychiatric conditions (22–24). Studies have found that rTMS not only improves sleep quality and optimizes sleep structure but also maintains therapeutic efficacy over pharmacological treatments and cognitive behavioral therapy and has emerged as a promising tool for treating sleep disturbances (22). Moreover, after 10 daily sessions of rTMS treatment in patients with primary insomnia, the concentrations of serum GABA and brain-derived neurotrophic factor (BDNF) were significantly higher than baseline (25). As we already know, GABA and BDNF both have a close relationship with sleep regulation (26–28). The change in metabolomics may be the potential mechanism of rTMS treatment in alleviating insomnia (28).

However, the implications of rTMS for insomnia in ASD patients have not been fully established. Only one study indicated that rTMS can alleviate sleep disturbances in ASD, which were assessed by the Children's Sleep Habits Questionnaire (CSHQ) (29). No randomized, double-blind, controlled studies were conducted to evaluate the efficacy of rTMS for insomnia through objective assessments such as PSG or actigraphy. Therefore, we aim to conduct a randomized, double-blind, sham-controlled trial to explore the effect of rTMS on insomnia with an objective assessment of ASD. Additional objectives include explorations of the effects of rTMS on ASD symptoms and the association between insomnia and ASD symptoms. We hypothesize that 1) rTMS applied to the right dorsolateral prefrontal cortex (DLPFC) can alleviate sleep quality and ASD symptoms and 2) metabolic changes may play a mediating role in sleep quality and ASD symptoms.

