#### Untargeted metabolomics analysis

We will collect whole blood using a heparin sodium anticoagulant tube and perform plasma separation as soon as possible. Briefly, the sample will be centrifuged at 3,000 rpm at 4°C for 10 min, the upper layer will be collected, and 0.2 mL/tube will be transferred into 2 mL centrifuge tubes. After the sample is labeled, it will be quick-frozen in liquid nitrogen for 15 min and stored at −80°C. Then, the sample will be incubated on ice for 5 min and centrifuged at 15,000 rpm for 5 min at 4°C. Some of the supernatant will be diluted to a final concentration containing 53% methanol with LC–MS grade water. The sample will be subsequently transferred to a fresh Eppendorf tube and then centrifuged at 15,000 g for 10 min at 4°C. Finally, the supernatant will be injected into the LC–MS/MS system for analysis. The raw data files generated by UHPLC–MS/MS will be processed using Compound Discoverer 3.1 (CD3.1, Thermo Fisher) to perform peak alignment, peak picking, and quantitation for each metabolite. These metabolites will be annotated using the KEGG database (http://www.genome.jp/kegg/), HMDB database (http://www.hmdb.ca/), and Lipidmaps database (http://www.lipidmaps.org/).

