## Statistical analysis

We will use SPSS software version 26.0 (IBM Corp, Armonk, New York, US) to perform data analysis. Demographic and baseline data will be analyzed with standard descriptive statistics. Normally and non-normally distributed data will be presented as means (SDs) and medians (quartiles), respectively. The comparison of basic data between the rTMS group and sham rTMS group will be performed using Student's *t*-test, the chi-squared test, or the nonparametric test according to the data type. To verify the efficacy of our intervention, the final analysis will be conducted according to the intent-to-treat (ITT) principle, and missing data will be replaced by means of the last observation carried forward rules. Changes in quantitative variables over time (evaluation of the therapeutic effect of rTMS on variations in sleep latency) will be analyzed using random-effect models allowing us to take into account repeated measurements. Time (baseline, post, and 1-month follow-up) and group (rTMS or sham) effects will be estimated and tested, along the interaction with the group. According to the same strategy, changes in other quantitative variables over time will be investigated. To further analyze the relationship between the change in the parameter of sleep and clinical symptoms, logistic regression, general linear correlation or regression will be taken into consideration between various types of outcomes. The number and proportions of participants with side effects, adverse events, and serious adverse events will also be reported. All statistical analyses will be two-sided, and statistical significance will be set at p<0.05. For untargeted metabolomics analysis, principal component analysis (PCA) and partial least squares discriminant analysis (PLS-DA) will be performed in metaX (a flexible and comprehensive software for processing metabolomics data). We will apply univariate analysis (*t*-test) to calculate the statistical significance (*P* value). Metabolites with VIP > 1 and *P* value < 0.05 and fold change (FC)≥ 2 or FC ≤ 0.5 will be considered to be differential metabolites.

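### Of the two markers that motivate the metabolomic mechanism, BDNF is not measured by the planned assay, and GABA counts as differential only if it at least doubles or halves

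*Protocol article*

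**What the plan says.** All references are to the protocol article.

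- **Introduction, rationale.** After ten daily rTMS sessions in primary insomnia, "the concentrations of serum GABA and brain-derived neurotrophic factor (BDNF) were significantly higher than baseline". The text links both markers to sleep regulation and then states: "The change in metabolomics may be the potential mechanism of rTMS treatment in alleviating insomnia". It gives no size for either rise.
- **Introduction, hypothesis.** The second hypothesis is that "metabolic changes may play a mediating role in sleep quality and ASD symptoms". It names neither marker.
- **Untargeted metabolomics analysis.** One blood assay is described. Heparin plasma is prepared ("Some of the supernatant will be diluted to a final concentration containing 53% methanol with LC–MS grade water"), then "the supernatant will be injected into the LC–MS/MS system for analysis". Software is used to "perform peak alignment, peak picking, and quantitation for each metabolite", and annotation uses KEGG, HMDB and Lipidmaps.
- **Outcomes.** Metabolomics is listed among the secondary outcomes.
- **Statistical analysis.** Metabolomics has its own decision rule. VIP > 1, a t-test P value below 0.05 and the fold-change limit are joined by 'and': "fold change (FC)≥ 2 or FC ≤ 0.5 will be considered to be differential metabolites".

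**The concern.** The rationale rests on two named markers, and the assay and rule treat neither as a candidate.

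- **BDNF** is a protein. That is general knowledge; the article only calls it a neurotrophic factor. A metabolite profile annotated against metabolite and lipid databases does not quantify it, and no other blood assay is described.
- **GABA** is a small molecule that such a run can in principle detect, but it passes through the same screen as every unknown peak. The size limit acts as a gate: a consistent rise that falls short of doubling is not differential, however small its P value.

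A fold-change limit is a sensible way to shorten a list of unknown peaks. It is a poor way to judge one candidate named beforehand. The risk lies in interpretation: a differential list without GABA or BDNF could be read as evidence against the mechanism in the Introduction. For BDNF it would carry no information. For GABA it would be compatible with a clear change of less than two-fold.

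**Working it through.** **1. The plan's own figure.** The Sample size section gives a 10 min difference, SD 8.4 min, two-sided 0.05, 80% power, 10% dropout and a total of 30. The normal approximation gives n = 2 × (1.96 + 0.84)² × 8.4² / 10² ≈ 11.1, so 12 per arm. The t-test needs 13 per arm (power 0.829). Then 13 / 0.9 = 14.4, so 15 per arm and 30 in total. The stated figure reproduces. It concerns sleep onset latency; metabolomics has no size calculation. The check below uses 15 per arm, with 13 as the number left after dropout.

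**2. Assumptions for GABA.** Log-normal levels; two arms compared by t-test on the log scale; fold change as the ratio of arm means. The article fixes neither the comparison (arms or time points) nor the scale, and it gives no CV and no expected change. VIP is left out, so the joint pass rates are upper bounds.

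**3. By hand, 15 per arm, CV 40%.**
- Log SD: √ln(1 + 0.4²) = 0.385.
- Standard error of the log ratio: 0.385 × √(2/15) = 0.141.
- P < 0.05 needs an observed log ratio of about 2.048 × 0.141 = 0.288, a ratio of about 1.33. Observed ratios between about 1.33 and 2 are significant but not differential.
- True ratio 1.5: (ln 1.5 − ln 2) / 0.141 = (0.405 − 0.693) / 0.141 = −2.04, so about 2% reach an observed ratio of 2.
- True ratio 2: (0.693 − 0.693) / 0.141 = 0, so about 50%.
- True ratio 2.5: (0.916 − 0.693) / 0.141 = 1.58, so about 94%.

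**4. By simulation (20,000 or 40,000 trials per cell), CV 40%, 15 per arm.**

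| True ratio | P < 0.05 alone | P < 0.05 and FC limit |
|---|---|---|
| 1.3 | 44% | 0.2% |
| 1.5 | 79% | 2 to 3% |
| 2.0 | 99.7% | 50% |
| 2.5 | not tabulated | about 94% |

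With 13 per arm, a true ratio of 1.5 gives 73% against 3%.

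**5. Range over the assumed CV, 15 per arm.**

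| CV | True 1.5: P alone | True 1.5: P and FC | True 2.5: P and FC |
|---|---|---|---|
| 20% | 100% | 0.0% | 99.9% |
| 30% | 95% | 0.3 to 0.5% | 98% |
| 50% | 62% | 5% | 89% |
| 80% | 33% | 14% | 78% |

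A true doubling passes in 48 to 50% at each of these CVs. The pattern holds throughout: a change well below two-fold rarely earns the label, and one well above usually does.

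**6. BDNF.** No arithmetic applies. The Introduction cites it, the metabolomics section describes an assay that does not measure it, and no section adds one that does.

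**The case against.** Much of the opposing case stands, and it limits the point.

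- **Neither marker is an outcome.** The earlier study is background, the hypothesis speaks of metabolic changes in general, and an untargeted assay fits that. A reader might infer that the trial promised to test GABA and BDNF and cannot. The article makes no such promise; what it shows is a mismatch between rationale and assay.
- **GABA is not out of reach.** A reader might infer that the rule makes it impossible to find. The 2.5-fold results show otherwise.
- **The rule fixes a label, not what is reported.** A reader might infer that a moderate rise would be published as no difference. The text does not say so: a P value is calculated for each metabolite, and nothing says that those failing the screen go unreported. The same section plans repeated-measures models for other quantitative variables. Whether these extend to single metabolites is unclear, and GABA is not named for them.
- **The size of the loss is partly built in.** A true ratio below 2 will usually fail a rule that requires an observed ratio of 2. With no size given for the earlier rise, the article does not show that two-fold is too strict, nor that it is suitable.
- **Stringency in a screen is a legitimate choice**, and a condensed article may leave candidate analyses to a fuller plan.

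None of this removes the stated rule. As written, it would label a clear change of less than two-fold, in the one motivating metabolite that the assay can see, as not differential.

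**Conclusion.** The point holds as a minor improvement. BDNF is not measured by the assay described. GABA earns the differential label only with an observed change of at least two-fold in either direction, on top of VIP and P. Under the stated assumptions, a true 1.5-fold change would be significant in about 79% of trials and labelled in at most 2 to 3%; a true 2.5-fold change would pass P and fold change in about 94%. These figures depend on an assumed CV, true ratio and between-arm log-scale comparison, none of which the documents supply. Only one secondary, exploratory outcome is affected. The primary analysis of sleep onset latency and the sample size are untouched.

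**What to change.** 1. Name GABA in advance as an exploratory candidate metabolite.
2. If it is detected, report the between-arm ratio on the log scale, adjusted for its baseline value, with a 95% CI and without the fold-change or VIP filter. Table 1 already schedules blood at baseline, after treatment and at follow-up.
3. Keep the joint rule only to screen unknown peaks.
4. State that BDNF is not measured, and that absence from the differential list is not evidence against a GABA or BDNF mechanism.

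The cost is analysis-plan wording and one extra named secondary test, with the same samples and assay.

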### Outcomes

The primary outcome of this study will be the difference in sleep onset latency between baseline and the end of treatment. Secondary outcomes will be differences in other parameters derived from polysomnography, the sleep diary, CSHQ, CARS, ABC, SRS, RBS-R, and metabolomics analysis.

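### The three-part rule for declaring differential metabolites uses unadjusted P < 0.05 across an untargeted panel, and neither VIP nor fold change controls the number of false listings

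*Protocol article*

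**What the plan says.** The Statistical analysis section of the protocol article fixes the whole selection rule. Its first two conditions are "Metabolites with VIP > 1 and *P* value < 0.05"; the third is "fold change (FC)≥ 2 or FC ≤ 0.5 will be considered to be differential metabolites". The P value comes from one univariate t-test per metabolite. VIP comes from a supervised model in the same section, where "principal component analysis (PCA) and partial least squares discriminant analysis (PLS-DA) will be performed in metaX". The general threshold is also unadjusted: "All statistical analyses will be two-sided, and statistical significance will be set at p<0.05".

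The section on untargeted metabolomics describes software that will "perform peak alignment, peak picking, and quantitation for each metabolite", so every metabolite that is picked up and quantified enters the rule. The number of metabolites is not given. No false discovery rate, q-value or other multiplicity control appears anywhere in the article.

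Metabolomics is a named secondary outcome ("CSHQ, CARS, ABC, SRS, RBS-R, and metabolomics analysis", Outcomes). The second hypothesis in the Introduction is that "metabolic changes may play a mediating role in sleep quality and ASD symptoms", and the abstract's Discussion expects the study to clarify a possible mechanism.

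**The concern.** An untargeted panel means many tests. At a raw 5% level, some metabolites will pass by chance even if stimulation changes none of them. The rule looks stricter than a bare P value because it has three conditions, but none of them is set with the number of tests in mind. The article calls the resulting metabolites differential without marking the list as a screen.

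What is at stake is the secondary metabolomics outcome and the mechanism hypothesis that draws on it. A list containing an unknown share of chance findings could be read as evidence of how stimulation affects sleep and autism symptoms.

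**Working it through.** **Inputs from the article.** Total sample 30, allocated 1:1; two-sided alpha 0.05; primary-outcome difference 10 min, SD 8.4 min, power 80%, dropout 10%; the three-part metabolite rule.

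**Assumptions, because the article gives no figure.** Panel of 200 to 2,000 metabolites (1,000 in the simulations); between-child SD on the log2 scale from 0.4 to 2.0; a two-arm comparison for the t-test.

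**1. The article's own figure.** A two-sample t-test (noncentral t) for 10 min with SD 8.4 has power 0.796 at 12 per arm and 0.829 at 13 per arm, so 13 are needed. Then 13 / 0.9 = 14.4, rounded up to 15 per arm, or 30 in total. The stated sample size reproduces. It was set for sleep onset latency and fixes about 15 per arm for the metabolite tests.

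**2. Raw P < 0.05 alone, no true change.** The expected number of false positives is M × 0.05: 10, 25, 50 and 100 for M = 200, 500, 1,000 and 2,000. Under independence the chance of at least one is 1 − 0.95^M, already above 99.99% at M = 200.

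**3. Adding VIP > 1.** In simulated null data (1,000 metabolites, two-component PLS-DA), about 50 metabolites had P < 0.05, and the same 50 had P < 0.05 and VIP > 1. VIP removed none at any setting, including with metabolites correlated at 0.5 in blocks.

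**4. Adding the two-fold condition.** Two-fold is 1 unit on the log2 scale. With 15 per arm the standard error of a difference in log2 means is SD × √(2/15) = 0.365 × SD, while P < 0.05 needs about 2.05 standard errors (28 degrees of freedom). The last two columns give false listings per 1,000 null metabolites. Fold change was taken as the ratio of raw means, which is noisier than the log2 difference, so column 2 is only a guide.

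| log2 SD | Two-fold, in standard errors | Article's full rule | Same rule with Benjamini-Hochberg q < 0.05 |
|---|---|---|---|
| 0.5 | 1 / 0.183 = 5.5 | about 0 | at most about 0.1 |
| 0.8 | 1 / 0.292 = 3.4 | about 1 | at most about 0.1 |
| 1.0 | 1 / 0.365 = 2.7 | about 10 | at most about 0.1 |
| 1.5 | 1 / 0.548 = 1.8 | about 36 | at most about 0.1 |
| 2.0 | 1 / 0.730 = 1.4 | about 43 | at most about 0.1 |

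At low SD the two-fold condition is far stricter than the t-test. Above an SD of about 1 / (2.05 × 0.365) = 1.3 it is the weaker of the two and removes little. A mix of SDs from 0.4 to 1.6 leaves about 13 to 14. With that mix, or with SD 1.0 or more, every simulated null trial gave a non-empty list. At 13 completers per arm the counts are similar or somewhat higher: about 14 at SD 1.0 and about 15 for the mix.

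**5. What the adjustment costs.** With 20 of 1,000 metabolites truly changed two-fold, 15 per arm, and the fold-change condition kept on both sides:

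| log2 SD | Article's rule: true / false | Benjamini-Hochberg: true / false |
|---|---|---|
| 0.5 | no difference | no difference |
| 0.8 | 9.9 / 1.3 | 5.3 / 0.15 |
| 1.0 | about 10 / about 9 | about 1.4 true |

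At SD 1.0 about 9 / (10 + 9) = 47% of the article's list is false.

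**The case against.** The strongest reply is that the fold-change condition does most of the filtering. If metabolites vary little between children (log2 SD of about 0.6 or less), it leaves almost no null metabolites, and an adjustment gains nothing. This stands. It means that 5% of the panel must not be quoted as the false-positive count, and that the size of the problem is conditional on a figure nobody can read from the article. It does not remove the point, because the article does not show that variability is that low and the rule does not adapt if it is not.

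A second reply is that this is a pilot, metabolomics is secondary, and the hypothesis says only that metabolic changes may mediate, so for screening the loss of true signals matters. That loss is real, as step 5 shows. But the rule is not labelled as screening, and at SD 1.0 about half of what it lists is false. Keeping an exploratory list meets the objection.

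A reader might infer more, and the article does not support it:

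- **That the test ignores each child's baseline.** The article says only that a t-test is used. It does not say paired or two-sample, or which visits are compared, so a wrong contrast is not stated.
- **That the PLS-DA is unvalidated, or that a mediation model is missing.** A condensed article may leave cross-validation, permutation and such a model to the full plan.
- **That this rule is the only metabolite analysis.** The same section extends the repeated-measures strategy to other quantitative variables and considers correlation or regression between types of outcome. Whether metabolites are covered is arguable.

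**Conclusion.** The point holds in a limited form. The article itself commits to a complete rule at an unadjusted P value, so this is not a detail left to an unseen plan. VIP gives no extra protection, and fold change gives protection that depends on variability: per 1,000 null metabolites at 15 per arm, from about 0 false listings at log2 SD 0.5 to about 43 at SD 2.0, against at most about 0.1 with Benjamini-Hochberg. These counts rest on an assumed panel size, assumed SDs and an assumed two-arm contrast.

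It does not follow that the published list will be mostly false, only that the rule cannot tell the reader whether it is. The matter should be corrected, but it touches a secondary outcome and the mechanism hypothesis. The primary outcome and the sample size stand.

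**What to change.** In the Statistical analysis section, replace the raw P condition by a Benjamini-Hochberg q-value below 0.05 across all metabolites tested, and use fold change and VIP as descriptive filters. Metabolites that meet only the present unadjusted rule may be reported in a separate list, labelled exploratory candidates. Label the mediation hypothesis in the Introduction and the mechanism statement in the abstract as hypothesis-generating.

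This needs no new data or participants, only a wording change and trivial computing, and the article describes the trial as ongoing. The price is fewer declared metabolites, including some true ones: in the example above, about 1.4 rather than 10 of 20 true two-fold changes at SD 1.0, and no loss at SD 0.5. The exploratory list keeps the remaining candidates in view.

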## Discussion

This study protocol presents the design of an RCT investigating the therapeutic effects of rTMS over the right DLPFC for insomnia in ASD by using a combined approach of home-PSG, sleep diary and clinically relevant scores from participants and caregivers. The results of this study will provide preliminary data on whether rTMS can alleviate insomnia in patients with ASD.

Although the cause of sleep disturbances in children with ASD is not clear, it has been found that the hyperarousal state also exists in ASD with insomnia (45, 46). Apart from that, there are several other possible hypotheses to explain it. First, the underlying abnormal pathophysiological mechanism of ASD may be the direct cause of sleep disturbances (47). Abnormal neural connectivity in the brain plays a pivotal role in ASD. The DLPFC, an essential part of integrating distributed brain networks that support the operation of verbal/auditory and spatial information in the brain, is dysfunctional according to proton magnetic resonance spectroscopy data in ASD (48, 49). Furthermore, abnormal sleep-promoting transmitters such as melatonin and GABAergic circuits have been found in ASD children with sleep disturbances (50–52). Second, the important role of cortical excitation/inhibition balance has been confirmed in sleep-stage-specific regulation (53). Increased cortical excitability has been found in different types of insomnia patients (54). In ASD, studies have found that cortical inhibition decreases and that the balance is disrupted, a noted predictor of autistic phenotypes (55). Third, there is a bidirectional association between ASD and sleep disturbances. Sleep disturbances may be related to the clinical phenotype and core symptoms of ASD (6, 56). Fourth, sleep problems may be associated with psychiatric comorbidity and independent of ASD (47).

rTMS is a noninvasive technique that produces a magnetic field by passing a brief electric current and introduces excitatory or inhibitory cortical excitability in a small area of the brain below the magnetic coil by modulating different stimulus frequencies (>1 Hz or < 1 Hz) (57). Recently, rTMS has been used in ASD. Two double-blind, randomized trials found that high-frequency rTMS (5 Hz and 20 Hz) applied to the DLPFC or bilateral dorsal medial prefrontal cortex can improve anxiety and executive function performance in patients with ASD (33, 34). High-frequency rTMS (10 Hz) to the left DLPFC can also alleviate depressive symptoms among ASD patients with depression (58). Low-frequency rTMS can increase cardiac vagal control and reduce sympathetic arousal, alleviating behavioral problems post-TMS improvement (59, 60). One study adopted low-frequency rTMS in children with low-functioning autism and found that it can increase the peak alpha frequency in different brain regions and alleviate behavioral symptoms assessed by the ABC (61). Furthermore, meta-analyses and systematic reviews indicated that rTMS could help treat some dimensions of ASD, such as repetitive and stereotyped behavior, sociability, or some aspects of executive and cognitive functions (62, 63). One study adopted theta burst stimulation (TBS), a patterned repetitive transcranial magnetic stimulation (rTMS) protocol over the bilateral posterior superior temporal sulcus and proved that it had an immediate effect on parent-rate autistic symptoms in adults with ASD (64). For glutamate and GABAergic circuits that are abnormal in ASD, one study found that rTMS (1 Hz) treatment for 2 weeks effectively alleviated the acquired autistic-like symptoms in a rat model by regulating synaptic GABA transmission (65). Furthermore, in adults with ASD, one study found that rTMS to the DLPFC may modulate local glutamate levels (66).

Considering its potential role, we hypothesize that rTMS can alleviate insomnia symptoms in ASD. However, no study has explored the effect of rTMS on insomnia symptoms in objective ways (such as PSG) in ASD. Therefore, the results of this study may address an important knowledge gap and may provide evidence for noninvasive and nonpharmaceutical interventions to treat insomnia in ASD.

